#### Secondary outcomes

The MuCCUA trial has a number of secondary outcomes including: infant mortality rate at 3, 6, 12, 18 and 24 months, proportion of neonatal low birth weight and low birth weight for gestational age, proportion of children with anaemia, cumulative incidence of morbidity (malaria, diarrhoea and pneumonia), primary caregiver’s knowledge, attitudes and practices related to perinatal and children’s caring practices including breast feeding and hygiene and sanitation, and women and children minimum dietary diversity.

#### Heterogeneity analyses

In addition to calculating the efficiency and cost-effectiveness of the MuCCUA trial, heterogeneity analysis will be conducted to assess how costs and impacts of the interventions are distributed among the target population. The economic evaluation will be stratified through subgroup analyses of the primary outcome based on differences of the study population characteristics. Disaggregation of the findings will be performed in subgroups per treatment arm, based on the two provinces and on the four communes of the study. The environment and way of living in each of the two provinces are slightly different in terms of, for example, distances between households’ compounds and health services. In the province of Cunene, households are very far apart from each other and they rely solely on themselves not having much interaction with other members of the communes. On the contrary, in the province of Huila, communities live closer together in villages and there are more interactions that exist between them. Socioeconomic status will not be included as a subgroup as we do not expect important differences because one of the inclusion criteria to participate in the study was to experience extreme poverty. In each of these subgroups, community group discussions will be carried out with different samples of participants according to their access to basic services and distance to the distribution points of the interventions.

#### Identification, measurement and valuation of resource use

The cost-efficiency and cost-effectiveness of the MuCCUA interventions will be measured from a societal perspective,^31 32^ taking into account costs incurred by the programme providers, namely the Institute of Local Development-Social Support Fund of Angola (FAS) and Vall d’Hebron Institute of Research (VHIR) (programme provider costs), ADECOS and by the beneficiaries who are intervention participants and their households. Resource use will be measured using financial expenditure data combined with micro-costing to allow for estimation of both financial and economic costs. All cost data will be collected prospectively from the launch of the MuCCUA community trial project for a 3-year (2022–2025) time period, and divided into start-up and recurrent costs. Table 1 provides an overview of the resource use and cost measures that are described in more detail further below.

**Table 1 T1:** Overview of resource use and cost measures included in the economic evaluation of the MuCCUA interventions

Perspective/cost category	Type of costs	Description	Source	Sample size
Programme/implementing agency	Direct	Costs of implementing the intervention	Project accounts of the implementing agencies Interviews with the project staff	N/A
	Indirect	Opportunity cost of donated items, volunteer time	Interviews with the project staff Project records on volunteer involvement Project accounts	N/A
Provider/health system (health providers)	Direct	Changes in demand/utilisation of nutrition and health services/costs of referrals	Baseline and endline cross-sectional surveys (for information on changes in cost of health-seeking behaviour) Project records for number of referrals	All participants from the study All referrals made in intervention and control clusters
	Indirect	Opportunity cost of increase in workload health workers in the study area Opportunity cost of the time spent by health workers participating in the intervention’s meetings	Time use survey with health workers Project records on health workers’ participation in intervention Project records on number of health strengthening meetings and attendants Published reports on local wage information based on skill category	A purposive sample of health workers will be selected for time use interviews N/A
Participants/households	Indirect	Opportunity cost of participation in the interventions, group meetings and home visits	Household survey Focus group discussions Qualitative interviews with a subsample of participants	All participants from the study A purposive sample of 6–9 participants per group discussion in each of the subgroups by intervention arm A purposive sample of 1–2 participants per each of the subgroups and intervention arms

MuCCUA, Mother and Child Chronic Undernutrition in Angola; N/A, not available.

#### Programme-related costs

Costs will be estimated using a mixed-methods approach combining costs estimated both from accounting records and using an ingredients approach.^43^ Resource use will be measured using financial expenditure data combined with micro-costing to allow for estimation of both financial and economic costs of each of the three intervention arms. An activity-based costing method will be applied to allocate and estimate financial costs per major programme activity, using accounting records and staff time allocation sheets based on the SEEMS-Nutrition standardised tools.^37^ The financial cost estimates will track payments, focusing on the resources coming from organisation, coordination and implementing partners including VHIR and FAS, and expenditure data for MuCCUA trial coming from Crescer Project expense reports. In addition, country salary scales will be used to estimate costs incurred by implementation partners (municipal supervisors, community activity assistants and medical staff). The ingredients approach will be used to estimate economic costs, costs not included in accounting records and indirect costs incurred by beneficiaries; these will be collected via key informant interviews, focus group discussions, structured questionnaires, household surveys and/or observation.^44^ Qualitative information will be collected through interviews from purposefully selected key informants from implementing organisations (VHIR, FAS), government officials (municipal supervisors, community activity assistants, FAS coordinators and health workers), beneficiaries and other members of the community. In order to use the activity-based costing methodology, staff time allocation will be assessed to estimate and allocate costs to activities. In addition, focus group discussions with beneficiaries will be performed to better understand opportunity costs to them and their communities from participating in the interventions. A total of 24 focus group discussions including 8–10 beneficiaries will be performed, two per trial arm in each of the four communes.

All costs will be collected prospectively from the project expense reports of the implementing and technical partners and entered into a programme costing tool in Microsoft Excel on an annual or monthly basis as appropriate. Data collection will be for the 3-year (2022–2025) time period from the launch of MuCCUA community trial. This method is recommended to assess the total costs of complex multisectoral nutrition and public health interventions that have multiple health and non-health effects.^29^

##### Financial or expenditure data

Financial costs will be collected by extraction of accounting sheets provided by financial officers of implementing partners (VHIR and FAS). Data from administrative financial records will be entered in Excel worksheets and assigned cost category codes for activities, inputs, thematic areas and timing of activities by implementation partners. For capital and start-up costs occurring at the start of the project, we will adjust financial records to reflect both financial and economic costs. Data obtained from interviews will be used to estimate averages and ranges of project-related time use by each type of implementing partner, and for project beneficiaries. We will estimate the total time for implementing partner and beneficiaries and value it with either the appropriate civil servant cost per minute (for government workers) or use a prevailing wage rate for rural or urban staff and beneficiaries. We will add in average costs of out-of-pocket expenses that have not been covered by the project. Labour and supply costs will then be coded (allocated) to the specific project activities and combined with the financial expenditure data to obtain total programme financial and economic costs. Capital and start-up costs will be annualised over their expected useful life.^45^

##### Donated items and opportunity costs

Some resources, such as donated items and volunteer time, are not routinely captured in project accounting records and will need to be identified and converted to economic costs using their market value.^45–47^ Common donated items are equipment or other capital items donated or owned by implementing agency. These will be identified through key informant interviews with the project staff.

Most of the volunteer time is related to designing messages for the standard of care intervention, where several meetings were held with experts who were volunteers. Detailed information on the number of meetings, their duration and participants is being documented by the project. The opportunity cost of the time invested by the experts will be estimated as a proportion of their salary or a salary equivalent using published national/local wage rate reports. In addition, some community members volunteer for the project mainly in sensitisation activities. The opportunity cost of volunteer time donated to programme implementation will be estimated using published national/local wage rate reports.

#### Public health provider cost/provider or health system cost

MuCCUA interventions are likely to increase demand for care services provided by community frontline health and nutrition workers such as ADECOS, community activity assistants and midwives, and other healthcare providers, such as malnutrition treatment centres or nutrition rehabilitation centres and primary health structures in the study area. In addition, there is a time cost of direct involvement in the project activities for the frontline workers and healthcare providers.

##### Cost of changes in utilisation of health and nutrition providers

Changes in the utilisation of health and nutrition services may occur in the form of increased demand as risk of malnutrition and other child illnesses are better identified in the communities by ADECOS. These changes in service provided by healthcare providers will be collected through questionnaires administered from study participants in both intervention and control areas at the MuCCUA endline household survey. The questionnaires ask participants on the frequency of attendance to the health posts, at baseline and at endline, and results will be compared before and after, and between arms.

##### Opportunity costs of MuCCUA activities/health workers

The MuCCUA interventions may increase the workload of health workers by increasing demand for their services. In contrast, the new community-based workers (or ADECOS) introduced by the MuCCUA trial, coupled with a stronger emphasis on preventive activities, may decrease the workload of existing health workers in the study areas. In addition, project activities include sensitisation and training sessions for healthcare providers in maternal, infant and young child health preventive activities in the intervention and control arms. Information on the number of meetings, their duration and participation is being documented by the project. The opportunity cost of involvement in the standard of care intervention or the value of the time spent in training by health workers will be measured as a proportion of their salary, using publicly available data on their salaries.

#### Participants and their household costs

MuCCUA interventions may influence participants and their households’ costs in a number of ways. Impacts on beneficiaries and their families may include changes in household food and non-food consumption patterns and spending (regarding variety, quantity or quality of food), changes in health-seeking behaviours and associated costs as well as time cost of participation in the interventions and of attending group meetings and home visits.

##### Opportunity cost of participating in the interventions

Participating in the MuCCUA interventions will incur some direct and indirect costs to beneficiaries and their families. These costs may include the cost of travelling to the health posts, food and cash distributions sites as well as the opportunity cost of time spent travelling. Basic travel time and costs will be measured using survey questions to all study participants during household surveys. In addition, the cost of attending community group meetings and engaging in household visits performed by the ADECOS will be estimated by collecting time allocation data from the individuals attending the group meetings at several household surveys. Focus group discussions with a subsample of participants purposively selected and equally distributed across the intervention and control arms will also be undertaken to explore any other opportunity costs to households and their communities of the implementation of the interventions. All these costs will feed into the overall cost analysis.

#### Cost-efficiency analysis

Total costs will be estimated for each of the three arms of the MuCCUA trial: standard of care, standard of care+nutritional supplementation and standard of care+cash transfers. We will estimate the cost-efficiency of MuCCUA trial by combining activity-specific cost data with routine data on programme outputs, in order to calculate the cost per output achieved. Numbers of index pregnant women, their newborn children until they are 24 months old and households reached by the intervention will be tallied by programme staff. Ratios of cost per woman, child and household reached will be calculated by dividing the total estimated intervention costs by the respective numbers reached.

#### Cost-effectiveness analysis

Economic evaluation will be conducted as a within-trial analysis using the intention-to-treat results, and will be presented in terms of incremental cost-effectiveness ratios (ICERs), calculated as the difference in total costs of standard care only (or comparator) versus nutritional supplementation or cash transfer divided by the difference in mean effects of each intervention versus control. As mentioned previously, ICERs will be calculated in terms of cost per stunting case prevented among children at 24 months old if there is a statistically significant difference in the outcome between intervention study arms.

The ICER will be calculated to compare the additional costs per improved outcome achieved in interventions, including nutritional supplements or cash transfers, compared with the standard of care intervention. Where feasible, we will disaggregate costs for different time frames, including start-up versus recurrent costs.

Sensitivity analysis will be performed to determine the extent to which the results of the analysis might change given plausible variation in study parameters related to cost drivers and stunting rates. To obtain an estimate of how costs could vary, a range of costs will be calculated based on different scenarios such as local costs scenario, product price or coverage. Univariate and multivariate probabilistic sensitivity analyses will assess effect of the main cost drivers on the results.

All costs will be presented in 2022 Angola kwanzas and in US dollars (USD). We will use the average monthly exchange rate for the year of cost data collection to convert costs into USD. Any costs encountered in the past will be inflated using the local gross domestic product deflator of Angola, before converting to USD. In addition, some expenses will be in euros and we will use the average exchange rate for the year of cost data collection to convert costs into USD. All costs will be adjusted for inflation using the Angolan Consumer Price Index and will be converted to 2022 USD using the purchasing power parity conversion factor for Angola. Moreover, the costs will be discounted using a standard discount rate of 3%, as recommended by WHO-CHOICE^48^ and the Gates/IDSi Reference Case for Economic Evaluation.^49^

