**Ethics and dissemination:**

This economic evaluation will provide useful information to the Angolan Government and other policymakers on the most cost-effective intervention to prevent stunting in this and other comparable contexts. The protocol was approved by the República de Angola Ministério da Saúde Comité de Ética (27C.E/MINSA.INIS/2022). The findings of this study will be disseminated within academia and the wider policy sphere.

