## Conclusion

The findings of this trial will provide evidence on which intervention package can have the greatest impact on preventing stunting in children under 2 years in Angola and improve comparability with other contexts. Robust understanding of the costs and benefits of these types of nutrition strategies is critical for priority setting and to motivate ongoing donor investment and government partnership.

The cost estimation of the different arms of the trial will complement the effectiveness results to provide useful information to the Government of Angola and other policymakers on the most cost-effective and cost-efficient intervention to prevent stunting. Additionally, this study aims to gain understanding on the cost drivers, to promote inclusion of economic evaluations in other nutrition intervention studies and to improve comparability with other contexts.

One of the limitations of the MuCCUA trial is that it is only powered to test the differences between each of the intervention arms and the comparison group, but not to test the differences between the two intervention arms. The latter would require a larger sample size and resources beyond those available for the trial. However, the possibility of a direct comparison between the interventions will be explored. The protocol has all necessary ethical approvals and the findings of this study will be disseminated within academia and the wider policy sphere.

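### The ICER formula pairs arm-total costs with mean effects, and its two ratios against standard of care do not by themselves show which of the three arms is most cost-effective

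*Protocol article*

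**What the plan says.** All references are to the protocol article.

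- **Formula.** The Cost-effectiveness analysis section describes a within-trial, intention-to-treat analysis whose ICER is "the difference in total costs of standard care only (or comparator) versus nutritional supplementation or cash transfer divided by the difference in mean effects", with every active arm set against the control arm.
- **Numerator.** The Cost-efficiency analysis section, immediately before, uses the term at arm level: "Total costs will be estimated for each of the three arms of the MuCCUA trial". It divides by a head count only for the cost-efficiency ratios: "Ratios of cost per woman, child and household reached will be calculated by dividing the total estimated intervention costs by the respective numbers reached". The ICER has no such step.
- **Intended unit.** The sentence after the formula says "ICERs will be calculated in terms of cost per stunting case prevented among children at 24 months old". Aim and objectives likewise asks for cost per case averted, from incremental costs and incremental outcomes. Primary outcome says that cases averted relative to control will be calculated at 24 months.
- **Comparator.** Aim and objectives and both ICER statements compare each active arm with standard of care. The second statement begins "The ICER will be calculated to compare the additional costs per improved outcome achieved in interventions" and names standard of care as the reference.
- **Use of the result.** The abstract's Ethics and dissemination paragraph says the evaluation will inform policymakers "on the most cost-effective intervention to prevent stunting in this and other comparable contexts", and the Conclusion repeats this aim. The Conclusion also says that the trial is not powered to compare the two active arms, and that "the possibility of a direct comparison between the interventions will be explored".

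**The concern.** There are two separate difficulties.

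First, the two halves of the ratio are on different scales. The numerator is money for a whole arm. The denominator is a mean per child: a difference in stunting proportions, or even in mean z-score, since the Primary outcome section names both. Their quotient is not a cost per case. If the arms hold different numbers of children, the arm totals would also differ for that reason alone.

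Second, the three packages are alternatives, and a policymaker picks one. Two ratios against a shared comparator show whether each active arm looks reasonable beside standard of care. They do not show what the extra effect of the dearer active arm costs over the cheaper one, or whether one active arm should drop out. A choice made from those ratios alone could favour the wrong arm without any visible error.

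**Working it through.** The article reports no ICER, so there is no figure to reproduce. The arm size is consistent: 3 × 480 = 1440 (Trial design).

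**1. Units**

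Let C be an arm's total cost, n its number of children and p its stunting risk, with 1 for the intervention and 0 for the comparator.

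- Literal rule: (C1 − C0) / (p0 − p1)
- Cost per case averted: (C1/n1 − C0/n0) / (p0 − p1)
- With equal arms the second becomes (C1 − C0) / [n(p0 − p1)], so the literal rule is too large by the factor n.

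Inputs from the article: n = 480 per arm; US$31.5 per month for households of four or more (Standard of care+cash transfer); an expected 13% reduction (Primary outcome). Assumptions: 24 months of transfers, one transfer per enrolled child, no other incremental cost, and 13% read as 13 percentage points, because the article does not say whether it is absolute or relative.

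- Arm-total difference: 480 × 31.5 × 24 = $362,880
- Literal rule: 362,880 / 0.13 = $2,791,385
- Cases averted: 480 × 0.13 = 62.4
- Consistent units: 362,880 / 62.4 = $5,815 per case averted

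Over 24 to 30 months, $24.7 to $31.5 per month and effects of 5 to 13 points, the consistent result runs from $4,560 to $18,900 per case. The literal result runs from $2.19 million to $9.07 million. The ratio between them is 480 throughout.

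**2. Unequal arms**

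Suppose two arms end with 480 and 440 children at the same $600 each (all assumed). The totals differ by 600 × (480 − 440) = $24,000, although the cost per child does not differ.

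**3. Comparator**

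The per-child increments over standard of care below are all assumed. A is the cheaper active arm and B the dearer.

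| Case | A: cost, effect | B: cost, effect | A vs standard of care | B vs standard of care | B vs A |
|---|---|---|---|---|---|
| 1 | $400, 0.10 | $850, 0.13 | 400/0.10 = $4,000 | 850/0.13 = $6,538 | (850 − 400)/(0.13 − 0.10) = $15,000 |
| 2 | $600, 0.08 | $850, 0.13 | 600/0.08 = $7,500 | 850/0.13 = $6,538 | (850 − 600)/(0.13 − 0.08) = $5,000 |

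In case 1 a payer willing to spend between $6,538 and $15,000 per case would find B acceptable against standard of care, but should not move from A to B. Choosing the lowest ratio is no remedy, since a payer willing to spend more than $15,000 should prefer B. In case 2 A is extendedly dominated: its step up from standard of care costs more per case than the further step to B. No planned step would report this.

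**The case against.** The strongest reply on units is that the formula should be read with the text around it. The next sentence, the objectives and the Primary outcome section all point to cost per case averted. An arm-total cost difference over a count of cases averted is a consistent ratio when arms are equal, and 480 per arm is planned. Total costs could also mean all cost categories summed. This stands to the extent that the intended quantity is clear. A reader might infer that the published ICER will be 480 times too large; the documents do not support that, because the factor arises only if one sentence is applied literally. What remains is that the formula disagrees with the stated objective, and that the nearest use of its numerator is at arm level.

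On the comparator, the planned ICERs do match the stated objectives, and the claim about the most cost-effective intervention appears only in the abstract and Conclusion. The lack of power between active arms is disclosed. A reader might infer that the plan compares arms only with standard of care and cannot identify the best one. Both go too far: a direct comparison is mentioned as a possibility, and the active-versus-active ICER follows from the same planned increments, as the table shows. The gap is that no such analysis is specified.

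A condensed article may leave detail to a fuller plan. But the formula is stated here, not omitted, and the background section on the trial says this paper is meant to set out the economic method in full. Limited power is a reason to show a wide interval, not to leave the comparison open.

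**Conclusion.** The point holds in this form. The ICER formula as written is inconsistent with the cost per case prevented that the article intends. Read literally it is larger by the arm size, 480 with equal arms, and it would absorb any difference in arm size. The planned ratios against standard of care do not by themselves support a statement about the most cost-effective intervention, and they can hide a high active-versus-active ICER or extended dominance. The comparator gap is the more consequential of the two, because nothing in the output would look wrong.

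The factor of 480 needs only the planned arm size and the literal reading. Every dollar result, the unequal-arm example and the 13-point reading of the effect are illustrations under the assumptions stated; none is a prediction for this trial. The article gives no willingness-to-pay threshold, so no particular wrong decision is shown.

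**What to change.** 1. Define the ICER as the difference in mean cost per enrolled child (intervention minus comparator) over the difference in stunting risk (comparator minus intervention), with both on the same intention-to-treat denominator. Equivalently, scale the cost difference to equal denominators and divide by cases averted. Name the denominator: the cost-efficiency ratios count those reached, cash is paid per household, and a household may contain more than one enrolled woman.
2. Replace the two pairwise ratios with a full incremental analysis of the three arms: rank by cost, remove dominated and extendedly dominated arms, and compare each remaining arm with the next cheapest remaining one.
3. Report cash versus nutrition as an estimate with its uncertainty, instead of leaving it as a possibility to explore.

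The cost is some wording and a little more analysis of data already being collected. The active-versus-active interval will probably be wide, as the trial is not powered for that comparison, and it should be presented as such.
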